## 8.2 Procedures for assessing Efficacy

Efficacy of the study treatments will be measured throughout the period of the study using both objective and subjective measures.

### 8.2.1 HbA1c

A glycosylated haemoglobin (HbA1c) level indicates the mean concentration of glucose in the participant's body over the preceding three month period. A blood sample (finger prick; approximately 3 drops) from all the participants will be collected at each site by the diabetes clinical care team for the analysis of HbA1c (as primary end point of the trial) prior to start of the randomised treatment then at 3, 6, 9 and 12 months.

The blood sample will be collected and analysed in line with local hospital laboratory standards.

Additionally, a blood sample will be collected in a tube identified by initials, study unique number and date/time of sample. The sample will be sent securely to a central clinical pathology laboratory at Alder Hey Children's NHS Foundation Trust for analysis to check standardisation of results from local hospital laboratories.

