### 4.2 Full Trial

#### Primary Endpoint

Glycaemic control (HbA1c) 12 months after diagnosis.

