|              |                                                           | Diagnosis                                                                         | Prior to start of treatment |                                                                              |               |               |                |
|              |                                                           | T0 =
Randomisation
(randomisation will be made within 14 days of diagnosis) |                             | (T0+3 months)                                                                | (T0+6 months) | (T0+9 months) | (T0+12 months) |
|              | Participant completed Health Utilities Index Mark 2 and 3 |                                                                                   | (X)                         | (X)                                                                          | (X)           | (X)           | (X)            |
|              | Parent completed Health Utilities Index Mark 2 and 3      |                                                                                   | X                           | X                                                                            | X             | X             | X              |
| Resource Use | RN completed CRF                                          |                                                                                   | X                           | X                                                                            | X             | X             | X              |

(X) – As indicated/appropriate.

1- Providing information, discussing the study and obtaining informed consent should occur as close to the time of diagnosis as possible, ideally between the time of diagnosis and Day 5 (diagnosis date +5).

2 - Measurement of blood glucose will be done by a glucose test at the time of diagnosis and measured as per local policy and the results recorded from patient medical records. It is measured by glucometer at remaining time points (refer section 8.2.3).

3 - Study Intervention –Randomised treatment should be commenced within 14 days of diagnosis

4– Hb1Ac will be collected and analysed according to local clinical practice and a sample sent for central analysis.

5 - Routine clinical tests will be conducted as part of routine clinical management and where appropriate results recorded from patient medical records.

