#### **Full Trial**

A sample size of 143 in each group will have 80% power to detect a difference in means of 0.50 assuming that the common standard deviation is 1.50 using a two group t-test with a 0.05 two-sided significance level. Allowing for 10% loss to follow up means we would need a total of 316 participants (158 per group). The estimate used for the standard deviation in the sample size calculation was taken from an audit at Alder Hey Children's NHS Foundation Trust based on children matching the inclusion criteria for this proposed study. A difference in HbA1c of 0.5% is widely recognized as the threshold used by the Food and Drug Administration (FDA) and pharmaceutical industry to determine effectiveness of any new oral hypoglycaemic agents. Current national studies investigating therapeutic interventions in children with diabetes were powered using this effect size. An improvement of 0.61% was detected in adults in the meta-analysis of studies included in the 2004 HTA report suggesting that in addition to this estimate being the minimum clinically important it is also a realistic difference to detect.

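### The primary HbA1c is the local-laboratory result, and the planned central-laboratory sample serves only as a check with no stated consequence: a small, cheaply removed loss of precision, without bias

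*Protocol*

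**What the plan says.** Section 4.2 gives the primary endpoint as HbA1c "12 months after diagnosis". Section 8.2.1 identifies the measurement: a finger-prick sample taken at each site from all participants, described as the primary end point, before randomised treatment starts and at 3, 6, 9 and 12 months. On where it is read, it says: "The blood sample will be collected and analysed in line with local hospital laboratory standards".

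The same section has a second sample sent to one central laboratory "for analysis to check standardisation of results from local hospital laboratories". Footnote 4 to Table 1 agrees: "Hb1Ac will be collected and analysed according to local clinical practice and a sample sent for central analysis". That footnote is attached to the HbA1c row, which is marked at baseline and at all four follow-up visits.

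Four other parts of the protocol bear on this:
- Section 9.2 randomises 1:1 in blocks of varying size, stratified by centre and age.
- Section 9.4 plans on an SD of 1.50: "The estimate used for the standard deviation in the sample size calculation was taken from an audit" at one hospital.
- Section 9.6 compares the arms with a two-group t-test and also mentions analysis of covariance for prognostic factors.
- Section 4.2 lists the percentage of participants with HbA1c below 6.5% as a secondary endpoint.

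**The concern.** Laboratories can differ systematically in the HbA1c they report. If each child's primary value comes from the local laboratory, those differences become part of the outcome. The planned t-test has no centre term, so it counts them as unexplained variation. The trial already intends to send a sample to a single laboratory at the same visits, which would avoid this.

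Two further things are at stake. First, the 6.5% endpoint has a fixed threshold, so a laboratory reading high or low moves children across it. Second, the standardisation check has no stated outcome. If it shows disagreement, an open-label trial will hold two versions of its primary endpoint with no rule in the protocol for which one counts.

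**Working it through.** **1. Reproduce the plan's figure.** Inputs from section 9.4: difference 0.50, SD 1.50, two-sided 0.05, 80% power, t-test. The exact two-sample t calculation gives 142.25, so 143 per arm, matching "A sample size of 143 in each group will have 80% power to detect a difference in means of 0.50". Power at 143 per arm is 80.2%. For 10% loss, 142.25 / 0.9 = 158 per arm, or 316 in total. The plan's arithmetic stands.

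**2. Add laboratory variation.** The protocol gives no between-laboratory SD. Assume s = 0.2, 0.3 or 0.4 HbA1c percentage points, on top of an SD of 1.50 within a laboratory.

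**3. What stratification does.** With equal numbers per arm within each centre, a laboratory's offset is added to both arms and cancels from the difference. The true standard error stays at

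1.50 × √(2/143) = 0.1774.

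The unadjusted t-test does not know this. It estimates its standard error from the total spread, about √(1.50² + s²) × √(2/143). With a critical value of 1.968 (284 degrees of freedom),

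power ≈ Φ[(0.50 − 1.968 × estimated SE) / 0.1774].

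| s | Total SD | Estimated SE | (0.50 − 1.968 × SE) / 0.1774 | Power |
|---|---|---|---|---|
| 0 | 1.500 | 0.1774 | 0.850 | 80.2% |
| 0.2 | 1.513 | 0.1790 | 0.833 | 79.8% |
| 0.3 | 1.530 | 0.1809 | 0.811 | 79.1% |
| 0.4 | 1.552 | 0.1836 | 0.781 | 78.3% |

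The loss is 0.4 to 1.9 percentage points. Treating offsets as independent from child to child, which ignores stratification, would give 79.5%, 78.7% and 77.5% and overstate it.

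**4. Check by simulation.** Assumed layout: 13 centres with 11 children per arm each (143 per arm), 40,000 trials per setting. The standard deviation of the estimated difference stayed between 0.177 and 0.178 for every s. Power of the unadjusted test was 79.8%, 79.2% and 78.3% for s = 0.2, 0.3 and 0.4. With a centre term it was 80.2%, 80.2% and 80.1%. A separate simulation with 15 centres of 20 children and s up to 0.5 gave a mean difference of 0.50 and type I error below 5%.

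**5. If the 1.50 already contains laboratory variation.** The within-laboratory SD is then √(1.50² − s²) = 1.487, 1.470 or 1.446. Central reading gives power of 80.9%, 81.8% or 83.0%. For local reading, put 1.50 × √(2/143) = 0.1774 in the numerator of the formula in step 3 and the smaller true SE (0.1758, 0.1738 or 0.1710) in the denominator. Power is 80.5%, 80.7% or 81.1%. The gap is again about 0.4 to 1.9 points, so the conclusion does not depend on what the audit SD contains.

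**6. The 6.5% cut-off.** If HbA1c is roughly normal with SD 1.50, the peak density is 0.399 / 1.50 = 0.266 per percentage point. A laboratory offset of 0.2 to 0.4 therefore moves at most 0.266 × 0.2 = 5.3% to 0.266 × 0.4 = 10.6% of that laboratory's children across the threshold. This is an upper bound. The actual share depends on how many children lie near 6.5%, which the protocol does not give.

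**The case against.** The strongest reply is that stratification by centre already deals with the problem. It largely does: there is no bias, and the difference itself is hardly any noisier. A centre term would recover most of the remaining loss without changing laboratory. Section 9.6 leaves room for covariate adjustment, and the choice of covariates properly belongs to the statistical analysis plan, which is not shown. How the standardisation check is acted on may be settled there too. This trial also calls itself pragmatic, and routine laboratories with a central check are a defensible choice. All of that stands, and it limits the weight of the point. It does not supply a reason to leave the single-laboratory value out of the primary comparison, and a centre term in the HbA1c model does nothing for the 6.5% classification.

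The pilot re-check of the SD in section 9.5 is a weaker safeguard. With 30 children, a 95% interval around an SD of 1.50 runs from about 1.2 to 2.0, which cannot separate 1.50 from 1.55.

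Two stronger readings are tempting. A reader might infer that the local result is exposed to staff who know the allocation. Section 8.2.1 says only that the clinical team collects the sample. It does not say that laboratory analysts know the arm, and HbA1c is an assay rather than a rated outcome. A reader might also infer that the planning SD holds no between-laboratory variance because it comes from one hospital. Section 9.4 does not say how the audit values were measured, so this is plausible but not established.

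**Conclusion.** The point holds as a cheap improvement of small size; it is not a serious flaw. The protocol fixes the local value as primary and gives the central value no role beyond checking. The cost is about 0.4 to 1.9 percentage points of power for an assumed between-laboratory SD of 0.2 to 0.4, plus possible misclassification at 6.5%. The sample-size arithmetic is sound, and nothing in the documents supports a claim of bias or inflated type I error.

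The figures rest on the assumed between-laboratory SD, near-equal arms within each centre, and one laboratory per centre. That the central sample covers every child is a fair reading of footnote 4 to Table 1. Section 8.2.1 states full coverage explicitly only for the local sample.

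**What to change.** Amend section 8.2.1 and footnote 4 to Table 1 to:
- name the central-laboratory HbA1c at the 12-month visit as the primary endpoint, and as the source for the percentage below 6.5%;
- use the local value, flagged, only where the central result is missing or unusable;
- report the all-local analysis as a sensitivity analysis;
- state that the central sample is taken from every participant.

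If the local value is kept as primary, state what will be done when the standardisation check shows disagreement, and include centre in the primary model.

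The cost is wording, since the samples and visits are already planned. The downside is that some central samples will be lost or unusable, and the fallback mixes assays for those children. Reporting how many there are in each arm would show whether that matters.

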## **8.2.2 Insulin requirements**

### **Participants receiving CSII**

Insulin usage data will be downloaded from the CSII pumps by the RN or the delegated person at 3-, 6-, 9- and 12- month study visit and forwarded electronically to the MC-CTU (guidance detailing the process will be provided to centres in the investigator site files. All the participants will record the insulin doses in the treatment held diaries used as part of routine practice.

### **Participants receiving MDI**

The RN will review the treatment diaries at each follow up visit and transcribe information from the diaries to the insulin usage CRF, which will be forwarded to the MC-CTU. At follow up visit the RN shall also contact the participant's GP to acquire the quantity of insulin prescribed for the participant. This will be compared to the quantities recorded by participants to guard against significant under-reporting. Any circumstances of non-compliance should be recorded on the participant's insulin usage CRF.

## **8.2.3 Blood glucose measurements**

At the time of diagnosis, blood glucose levels of all the participants will be measured according to local policy. At the remaining time points blood glucose will be measured using a glucometer (see section 7.3 for glucometer supply details). Data from the glucometers will be downloaded by the diabetes research nurse or the delegated person at 3-, 6-, 9- and 12-month study visit and forwarded electronically to the MC-CTU (guidance detailing the process will be provided to centres in the investigator site files).

## **8.3 Procedures for Assessing Safety**

### **8.3.1 Adverse events:**

Participants will be monitored for treatment related adverse events (AEs) and treatment related serious adverse events (SAEs) (see section 10 for details). They will be issued with a diary to document home episodes of severe hypoglycaemia and diabetic ketoacidosis. Treatment diaries and telephone logs will be assessed at each study visit for any treatment related AEs and related SAEs.

For this study we will also monitor adverse events related to the disease under study.

In addition to self-reporting, local hospital databases will be interrogated at each clinical assessment to ascertain whether the subject has been treated for a related SAE in the preceding three months. Related AEs (including incidences of severe hypoglycaemia and diabetic ketoacidosis) and related SAEs will be reported as described in section 10.6.

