### **8.1 Schedule for Follow-up**

The study duration of each participant (including follow-up period) is one year from the date of randomisation. All participants will be reviewed at the diabetes outpatient clinic every three months as per standard clinical practice and will have four follow up visits at 3-, 6-, 9- and 12- months from randomisation. Participants will have a flexible window of  $\pm 15$  days to report for each follow up visit.

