### Serious ARs/AEs/SUSARs/RUSAEs

SARs, SAEs, SUSARs and RUSAEs will only be reported for participants where consent has been obtained and the causal relationship has been assessed and judged by the investigator to be related to the trial treatment (see section 10.4) and / or disease under study (see section 10.3), which occurs from the start of randomised treatment until final follow-up visit at 12 months post-diagnosis. They should be reported to the MC-CTU using the related SAE form **within 24 hours** of the local site becoming aware of the event.

The related SAE form asks for the nature of event, date of onset, severity, corrective therapies given, outcome and causality. The responsible investigator should sign the causality of the event. Additional information should be sent within 5 days if the reaction/event has not resolved at the time of reporting.

Refer to section 10.9 and 10.10 for further details on the reporting procedures and the responsibilities of the investigators and the MC-CTU respectively. Any questions concerning adverse event reporting should be directed to the MC-CTU in the first instance. A flowchart is given below to aid in determining reporting requirements.

**All hospital admissions** will be reported as part of the routine baseline and follow-up CRFs and using electronic databases. Only report hospital admissions using the related SAE CRF if they occur in the specified time frame and are judged to be related to the trial treatment.

**All deaths** that occur between the time of consent and the 12 month follow-up should be reported to the MC-CTU using the death CRF **within 7 days** of the clinical research team becoming aware of the event. If a patient's death has been assessed and judged by the investigator to be related to the trial treatment (see section 10.4), a related SAE CRF should also be completed.

[figure not shown]

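### The hospital-database check for related SAEs looks back only three months, although consecutive visits can be about four months apart, so some follow-up days can go unsearched

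*Protocol*

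**What the plan says.** Protocol section 8.3.1 describes several routes for finding adverse events. Families keep a diary of home episodes of severe hypoglycaemia and diabetic ketoacidosis, and "Treatment diaries and telephone logs will be assessed at each study visit for any treatment related AEs and related SAEs". A further check follows: "In addition to self-reporting, local hospital databases will be interrogated at each clinical assessment", the purpose being "to ascertain whether the subject has been treated for a related SAE in the preceding three months". The look-back is a fixed length. It is not tied to the date of the last search, and nothing extends it after a late or missed visit.

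Section 8.1 says that participants "will have four follow up visits at 3-, 6-, 9- and 12- months from randomisation" and gives each visit a tolerance of 15 days either way ("Participants will have a flexible window of" ±15 "days to report for each follow up visit").

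Section 10.6 requires related SAEs to be reported over one continuous period, from the start of randomised treatment to the final 12-month visit. The same section says that all hospital admissions "will be reported as part of the routine baseline and follow-up CRFs and using electronic databases", with no look-back limit. Severe hypoglycaemia and ketoacidosis are secondary endpoints, both as incidences (section 4.2).

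**The concern.** A fixed look-back run at movable visits cannot cover a continuous period. Whenever two visits are more than three months apart, the first days of that interval lie outside both searches. Each visit can be in its window and each search done as written, and the days are still unsearched.

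The search is the dedicated SAE check that supplements the account of families who know their allocation. Some hospital-treated episodes of severe hypoglycaemia or ketoacidosis, both counted as secondary endpoints, could fall in the unsearched days. The count would then rest on the other routes alone for that time. Children with irregular attendance have the most unsearched time.

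**Working it through.** The plan gives no figure for search coverage, so there is none to reproduce. The check is interval arithmetic.

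**Inputs**
- Look-back L = 3 months (section 8.3.1). With a year of 365.25 days, L = 365.25 / 4 = 91.3 days.
- Scheduled visits at 3, 6, 9 and 12 months from randomisation: days 91.3, 182.6, 273.9 and 365.25 (section 8.1).
- Window ±15 days at each visit (section 8.1).
- Unsearched days in an interval = max(0, interval − L). The first interval is counted from randomisation.

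**Largest single interval.** A visit 15 days early followed by one 15 days late: 91.3 + 15 + 15 = 121.3 days, or 121.3 / 30.4 = 3.99 months. Unsearched: 121.3 − 91.3 = 30 days. For the first interval only the month-3 visit can move, so the maximum is 15 days.

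**Worst pattern within the windows.** Offsets −15, +15, −15, +15 give intervals of 76.3, 121.3, 61.3 and 121.3 days. Unsearched: 0 + 30 + 0 + 30 = 60 days. Follow-up then lasts 365.25 + 15 = 380.25 days, and 60 / 380.25 = 15.8%.

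**Average, assuming visit dates independent and uniform in the window.** The documents give no distribution of visit dates, so this is an assumption.
- First interval: the excess over L is uniform on −15 to +15, and its mean positive part is 15 / 4 = 3.75 days.
- Each later interval: the excess is a difference of two such offsets, triangular on −30 to +30, and its mean positive part is 30 / 6 = 5 days.
- Total: 3.75 + 3 × 5 = 18.75 days, and 18.75 / 365.25 = 5.1% of the year.
- A child has no gap only if all four offsets are at or below zero and each is no later than the one before: (1/2)^4 / 4! = 1/384. So 99.7% would have some gap, but this counts gaps of any length, including a single day.

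**One missed visit, others on time.** The interval is 2 × 91.3 = 182.6 days. Unsearched: 182.6 − 91.3 = 91.3 days, or 91.3 / 365.25 = 25% of the year. If the missed visit is month 6 or 9 and both neighbours can move by 15 days, the range is 91.3 − 30 = 61 to 91.3 + 30 = 121 days. The documents give no rate of missed visits.

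**After the fix.** If each search starts where the last one ended, the unsearched time up to the latest search is 0 days for any visit pattern, including a missed visit that is followed by a later search.

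**The case against.** The strongest reply is that the search is one route among several, and that unsearched days are not missed events. Section 10.6 captures all admissions on the follow-up CRFs and through electronic databases. Under section 10.1.1 any inpatient admission is serious regardless of length, so an event that is serious because of hospitalisation should also appear there. Diaries and telephone logs are reviewed at every visit, and sites must report related SAEs within 24 hours of learning of them. This stands, and it narrows the exposure. It does not close the gap, because section 10.1.1 also allows an event to be serious without admission. The Patient Administration System extract in section 8.4.2 is requested only 12 months after a centre's last randomisation and lists ward, dates and bed days, with no diagnosis item.

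It can also be said that three months is shorthand for the time since the last visit. That is a plausible intention, but the sentence states a length, and a site that applies it literally follows the protocol.

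Three stronger readings are tempting and are not supported:
- *The search is the only check that does not rest on the family's account.* Section 10.6 provides admission data from electronic databases, and section 7.5 has contact with the clinical service logged.
- *The loss differs between arms.* The windows are the same in both arms, and the documents give no missed-visit rate, by arm or overall.
- *Table 1 lets sites omit the two endpoint events, because it marks them as indicated or appropriate, so that none cannot be told from not asked.* The mark can equally mean that an event is recorded when one occurs. Section 8.3.1 has the diaries assessed at each visit without qualification, and section 13.2 requires an explicit entry where a question was not asked. The CRF itself is not shown.

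**Conclusion.** The point holds for the database search and not for SAE capture as a whole. With every visit in its window, up to 30 days in an interval and 60 of about 380 days over follow-up can go unsearched. The mean of about 19 days rests on assumed uniform visit timing. After one missed visit, with the others on time, about 91 days are unsearched even though the search rule is followed.

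These are calendar days and not a proportion of events; the documents do not allow the number of missed events to be estimated. The likely consequence is some under-counting of serious events that were treated without admission and not otherwise reported, in both arms alike as far as the documents show. The primary HbA1c comparison is not affected. The defect is modest, but it sits in a stated rule that supports two secondary safety endpoints.

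**What to change.** In section 8.3.1, replace the three-month limit with: *since the previous completed search (since the start of randomised treatment at the first search)*. The searches, ending with the one at month 12, then cover the whole reporting period set in section 10.6, including time left by a missed earlier visit. No change to Table 1 is needed.

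The cost is one phrase. The same search is run at the same visits with a different start date, and the site must note the date of each completed search. Treatment, visits and sample size are untouched.
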